# Comparing conVEntional RadioTherapy with stereotactIC body radiotherapy in patients with spinAL metastases: study protocol for an randomized controlled trial following the cohort multiple randomized controlled trial design

**DOI:** 10.1186/s12885-016-2947-0

**Published:** 2016-11-21

**Keywords:** VERTICAL trial, Randomized controlled trial, Cohort multiple Randomized Controlled Trial design, Spinal metastases, Bone metastases, Pain, Stereotactic body radiotherapy

## Abstract

**Background:**

Standard radiotherapy is the treatment of first choice in patients with symptomatic spinal metastases, but is only moderately effective. Stereotactic body radiation therapy is increasingly used to treat spinal metastases, without randomized evidence of superiority over standard radiotherapy. The VERTICAL study aims to quantify the effect of stereotactic radiation therapy in patients with metastatic spinal disease.

**Methods/design:**

This study follows the ‘cohort multiple Randomized Controlled Trial’ design. The VERTICAL study is conducted within the PRESENT cohort. In PRESENT, all patients with bone metastases referred for radiation therapy are enrolled. For each patient, clinical and patient-reported outcomes are captured at baseline and at regular intervals during follow-up. In addition, patients give informed consent to be offered experimental interventions. Within PRESENT, 110 patients are identified as a sub cohort of eligible patients (i.e. patients with unirradiated painful, mechanically stable spinal metastases who are able to undergo stereotactic radiation therapy). After a protocol amendment, also patients with non-spinal bony metastases are eligible. From the sub cohort, a random selection of patients is offered stereotactic radiation therapy (*n* = 55), which patients may accept or refuse. Only patients accepting stereotactic radiation therapy sign informed consent for the VERTICAL trial. Non-selected patients (*n* = 55) receive standard radiotherapy, and are not aware of them serving as controls. Primary endpoint is pain response after three months. Data will be analyzed by intention to treat, complemented by instrumental variable analysis in case of substantial refusal of the stereotactic radiation therapy in the intervention arm.

**Discussion:**

This study is designed to quantify the treatment response after (stereotactic) radiation therapy in patients with symptomatic spinal metastases. This is the first randomized study in palliative care following the cohort multiple Randomized Controlled Trial design. This design addresses common difficulties associated with classic pragmatic randomized controlled trials, such as disappointment bias in patients allocated to the control arm, slow recruitment, and poor generalizability.

**Trial registration:**

The Netherlands Trials Register number NL49316.041.14. ClinicalTrials.gov registration number NCT02364115. Date of trial registration February 1, 2015.

## Background

Bone metastases are a frequent distant manifestation of cancer, with the spinal column being the most common site [1]. Spinal metastases can induce cancer-related pain, mechanical instability, and neural compression, thereby causing morbidity and impacting on quality of life (QOL). Treatment is aimed at pain relief and prevention of neurological deficits. The treatment for most patients with symptomatic spinal metastases is standard external beam radiotherapy [2], which is moderately effective: around 60% of patients who undergo external beam radiotherapy experience pain relief [3]. Furthermore, pain relief is often incomplete with complete pain response rates ranging from 0 and 23% [3] and one in five patients needs re-irradiation [4]. Escalating the dose to the metastatic site might improve the pain response and prolong the duration of pain relief [5]. Dose escalation to spinal tumors using standard radiotherapy is complicated by the low tolerance of the spinal cord to radiation. Stereotactic body radiotherapy (SBRT) is able to deliver precise high-dose radiation to spinal metastases in single or multiple fractions, while sparing surrounding healthy tissues. Phase I and II studies have suggested that, for selected groups of patients, SBRT for spinal metastases may be accurate, safe, and effective [5, 6], with complete pain response in 54% of patients six months after SBRT [7]. Other authors even reported overall pain response rates around 90% [8–10]. To date however, no randomized controlled studies have been performed so equipoise still exist on the effectiveness of SBRT in comparison to standard radiotherapy. Therefore, we designed a pragmatic randomized controlled trial to compare conVEntional RadioTherapy with stereotactIC body radiotherapy in patients with spinAL metastases (VERTICAL) following the CONSORT statement [11].

## Methods/design

### Study design

This study is conducted within the Prospective Evaluation of interventional StudiEs on boNe meTastases (PRESENT) cohort [12]. All patients with bone metastases referred to the departments or radiation oncology or orthopedic surgery of the University Medical Center Utrecht are asked to participate in this prospective, observational cohort. Baseline and follow-up data are collected from clinical files, and patient-reported outcomes (PROMs, i.e. a pain inventory and QOL questionnaires) are collected at fixed time intervals. This study follows the cohort multiple randomized controlled trial (cmRCT) design as described by Relton and colleagues [13].

### Patient recruitment

At enrollment, patients give informed consent for collection of clinical and survival data, and can opt-in to provide PROMs. In addition, in a separate question, we ask patients for their broad consent for future randomization in trials that will investigate the effectiveness of experimental treatments [14]. Patients within the PRESENT cohort who meet the VERTICAL inclusion criteria (Table 1) are identified as a sub cohort of eligible patients. Eligible patients are PROMs-providing participants of the PRESENT cohort, have untreated symptomatic spinal metastases, and have given consent for broad randomization to experimental interventions. Patients are excluded if they are not able to undergo SBRT, have severe or progressive neurological deficits, received previous radiotherapy or surgery to the index site(s), or have a life expectancy less than three months. After a protocol amendment on September 23, 2015 to adjust to developments in clinical practice, also patients with non-spinal bony metastases are eligible.

**Table 1 Tab1:** Selection criteria for the VERTICAL study

Inclusion criteria	Exclusion criteria
Participant in PRESENT cohort	Lesion in C1, and C2
Filling out PRESENT-questionnaires	Contraindication for MRI if MRI is indicated
Broad consent for randomization to experimental interventions	Radiosensitive histology such as multiple myeloma
Histologic proof of malignancy	Unable to undergo SBRT treatment
Imaging evidence of bone metastases	Patient with < 3 months life expectancy
For spinal lesions, per lesion no more than 3 consecutive spine segments involved with one unaffected vertebral body above and below	Chemotherapy or systemic radionuclide delivery within 24 h before and after SBRT
No more than 2 painful lesions needing treatment	Previous EBRT or SBRT to same level
For spinal lesions, no compression of spinal cord	For spinal lesions, unstable spine requiring surgical stabilization
No or mild neurological signs^a^	Severe, worsening or progressive neurological deficit
KPS > 50 and pain score > 3^b^	

*VERTICAL* randomized controlled trial comparing conVEntional RadioTherapy with stereotactIC body radiotherapy in patients with spinAL metastases; *PRESENT* Prospective Evaluation of interventional StudiEs on boNe meTastases (PRESENT) cohort; *MRI* magnetic resonance imaging; *SBRT* stereotactic body radiotherapy; *EBRT* external beam radiotherapy; *KPS* Karnofsky performance score

^a^radiculopathy, dermatomal sensory change, and muscle strength of involved extremity is Medical Research Counsil (MRC) 4/5

^b^on a scale from 0 to 10

### Random selection

Eligible patients are randomly selected from the sub cohort on a 1:1 basis with varying block sizes (*n* = six or eight) using an in-house randomization computer program. The radiation oncologist will offer the experimental intervention (i.e. SBRT) to the randomly selected patients. If they accept the treatment offer, they will sign informed consent for participation in the VERTICAL study. Patients who refuse the SBRT will receive care as usual (i.e. standard radiotherapy). According to the cmRCT design, patients in the sub cohort who are not randomly selected will not be informed about the experimental intervention, nor will they be informed about their participation in the control arm of the VERTICAL study. Outcomes in randomly selected patients are compared with the outcomes in eligible patients not randomly selected who received standard radiotherapy (Fig. 1).

**Fig. 1 Fig1:**
[figure not shown]
Study design VERTICAL study A large observational cohort of patients with bone metastases is recruited and their outcomes regularly measured (*dark blue* box). Patients within the PRESENT cohort who meet the VERTICAL inclusion criteria are identified as a sub cohort of eligible patients (*light blue* box). Randomly selected patients (*orange* box) are offered the SBRT intervention. The outcomes of these randomly selected patients (i.e. the intervention arm) are then compared with the outcomes of eligible patients not randomly selected who receive standard of care (i.e. the control arm, *brown* boxes)

### Standard radiotherapy

Standard radiotherapy for symptomatic bony metastases consists of single fraction external beam radiotherapy of 8 Gray (Gy). The radiation oncologist might however choose a multi-fraction regime of 30 Gy in 10 fractions if the patient has a favorable primary tumor (i.e. breast or prostate cancer), a Karnofsky performance score (KPS) of 80–100%, and absence of visceral or brain metastases. The radiation dose distribution usually consists of a single field in posteroanterior direction with the normalization point (100% isodoseline) at 6 cm for a 6 MV photon beam and at 6 or 7 cm for a 10 MV photon beam. The vertebral body should at least receive 80% of the prescribed dose. If necessary, a field in anteroposterior direction is added to the posteroanterior field. Metastases in the cervical spine are usually treated with two lateral opposing fields. The leafs of the multileaf collimator are used to adjust the shape of the treatment field. Prior to treatment, cone beam computed tomography (CBCT) scan images are obtained to verify that the position of the patient is correct with regard to the planning computed tomography (CT). Currently, our department is working on the clinical implementation of auto-planning for single fraction treatment of patients with bone metastases. Automatic treatment plans will then be delivered to the spinal metastases using intensity-modulated radiation therapy (IMRT) technique.

### Stereotactic body radiotherapy

Patients in the experimental arm undergoing SBRT are immobilized with an S-frame thermoplastic mask in case of skull or cervical spine tumors extending to the upper thoracic (T3) vertebral body. In case of lower thoracic and lumbar lesions, and rib and pelvic lesions, they are immobilized using a vacuum mattress (BlueBAG™, Elekta, Stockholm, Sweden). Magnetic resonance imaging (MRI) is used to delineate the gross tumor volume (GTV), clinical target volume (CTV), and the organs at risk (OAR). We use MRI guidance to deliver stereotactic radiotherapy to the visible metastasis (i.e. GTV) exclusively. With the aid of T1 weighted, T2 weighted, and diffusion weighted imaging (DWI) sequences, it is possible to delineate the GTV accurately [15, 16]. Adjacent normal appearing bone may harbor subclinical disease and could potentially serve as a source for a local recurrence [17]. Therefore, the bony compartment containing the GTV (i.e. the CTV, which consists of the entire vertebral body, pedicle, transverse process, lamina, or spinous process) is prescribed 8 Gy in order to treat subclinical disease whereas the metastasis receives 18 Gy (Fig. 2). This *simultaneous integrated boost* approach has the potential advantage of lowering the risk of vertebral compression fractures by sparing the unaffected, healthy bone tissue surrounding the metastasis while also treating subclinical disease. When necessary, an equivalent dose may be given using another fractionation schedule: 30 Gy in three fractions to the visible metastasis with 15 Gy in three fractions to the bony compartment or 35 Gy in five fractions with 20 Gy in five fractions to the bony compartment. Possible reasons to fractionate the dose might be proximity of visible metastasis to the spinal cord or more than two consecutive spine segments involved. Treatment planning is performed on pre-treatment CT and MRI scans that are co-registered to yield information on all relevant structures for assessing dose distribution. Volumetric modulated arc therapy (VMAT) treatment plans are generated for SBRT patients. Dose constraints are set for the OAR based on institution specific guidelines. These constraints, and particularly the constraint of the spinal cord, are of primary concern. If necessary, dose deliverance to the GTV will be limited in order to meet these constraints [18]. For all patients, an online CBCT scan is acquired with the patient in treatment position on the treatment couch just before start of the irradiation. The CBCT scan yields the exact position of the bony anatomy and is registered to the pre-treatment CT and MRI data. The alignment of the patient, or more specifically the affected vertebra bodies, on the CBCT scan is compared with the pre-treatment CT and MRI scans. After possible correction a second CBCT is performed between the two VMAT arcs. A third CBCT is taken post-treatment to document stability of the target during treatment.

**Fig. 2 Fig2:**
[figure not shown]
Standard radiotherapy and stereotactic body radiotherapy Comparison of a conventional radiation dose distribution using standard radiotherapy (*left*) with a spinal stereotactic radiotherapy simultaneous integrated boost distribution (*right*) in a patient with a T4 vertebral body metastasis from breast cancer

### Primary endpoint

Primary endpoint of this study is complete or partial pain response at three months. Pain response is defined according to the International Bone Metastases Consensus Endpoints for Clinical Trials (Table 2) [19]. A pain score of zero with no concomitant increase in analgesic intake compared to baseline is defined as complete response. Partial response is pain reduction of at least two points on a scale of 0–10 without increase in analgesic intake and/or analgesic reduction of at least 25% from baseline without an increase in pain. Pain progression is defined as an increase in pain score of at least two points above baseline with stable analgesic use and/or as an increase of at least 25% in analgesic use compared to baseline with at least stable pain scores. All responses not captured with complete and partial response or pain progression are considered indeterminate response. Pain is measured by the Brief Pain Inventory (BPI), which has been validated for use in advanced cancer patients to assess pain and functional interference stemming from bone metastases [20].

**Table 2 Tab2:** Response rate to radiotherapy according to the international consensus [19]

Responders	
Complete response	Pain score of 0 and stable or reduced OMED
Partial response	Pain reduction of 2 points on a 0–10 scale or more and/or OMED reduction by 25% or more
Non-responders	
Pain progression	Increase of 2 points on a 0–10 scale or more above baseline, and/or OMED increased by 25% or more
Indeterminate response	Any response including stable disease that is not captured by complete or partial response or pain progression

*OMED* daily oral morphine equivalent

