### Secondary endpoints

Secondary endpoints include local tumor control, duration of pain response, toxicity, vertebral compression fractures, QOL, and overall survival. Evaluation of local tumor control will be based on imaging acquired during follow-up. Duration of pain response starts at response until pain progression or end of follow-up using information provided by the BPI. A radiation oncologist records toxicity according to the National Cancer Institute’s Common Terminology Criteria for Adverse Events, version 4.0 [21] six weeks after radiation treatment. Toxicity occurring after 6 weeks, (serious) adverse events (SAEs), and hospitalization are registered in the context of the PRESENT cohort. Information about toxicity is based on clinical follow-up data and biannual patient-administered questionnaires on health status and hospitalization. All patients in the SBRT arm undergo an additional MRI scan six months after radiation in order to assess vertebral compression fractures. Since most compression fractures occur four months after radiation treatment [22], this 6-month-MRI captures most incidents. In case of clinical suspicion of a vertebral compression fracture, obtaining the MRI scan will be advanced as deemed appropriate. Quality of life is measured by the EORTC QLQ-C15-PAL general questionnaire [23] and the bone metastases-specific module, the EORTC QLQ-BM22 [24]. The EORTC QLQ-C15-PAL is an abbreviated 15-item version of the EORTC QLQ-C30 specially developed for use in palliative care. In order to evaluate the cost-effectiveness, patients are also provided with the EQ-5D questionnaire. Patients fill out these QOL questionnaires and the BPI before the start of radiation treatment (baseline) and after one, two, three, and six months, and every six months thereafter. The BPI is provided after two and six weeks as well. We make use of the digital patient tracking system PROFILES, so patients are able to complete the questionnaires online after secured login [25]. Overall survival is monitored within the PRESENT cohort by clinical follow-up and via an electronic link with the Municipal Personal Records Database.

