### Data analysis

Data will be analyzed according to the intention to treat principle. Data of eligible patients who were randomly offered stereotactic radiotherapy will be compared with eligible patients who were not randomly selected and received standard radiotherapy. In case of dropout (i.e. patients not surviving longer than three months or patients unable to provide pain scores and analgesic use), a worst-case analysis will be performed: dropped-out patients will be classified as non-responders. In case of substantial refusal of the SBRT offer in the intervention arm, instrumental variable analysis will be used to account for non-compliance [26]. The primary outcome (i.e. proportion of patients with response to radiotherapy) will be presented in absolute numbers and proportions. Differences in pain response will be compared by χ2 test. If randomization fails, imbalances between baseline characteristics will be adjusted by logistic regression analysis. Differences in duration of response and overall survival will be analysed by Kaplan-Meier analysis and log rank test. Toxicity will be presented as the overall incidence of grade 3–4 toxicity and incidence of vertebral compression fractures. Differences will be tested with the χ2 test. A comparison in QOL will be made between the baseline QOL and at predefined intervals after treatment. A change of 10% of the scale breadth will be considered a clinically relevant change of QOL [27]. Data will be presented as improved (≥10% increase), stable, or worsened (≥10% decrease) QOL. We will evaluate the pattern of QOL as a continuous outcome over time using mixed models. Differences with a *P*-value <0.05 will be considered statistically significant. We have planned to perform an interim analysis after inclusion of half of the patients (i.e. 55 patients) when they have completed their follow up (i.e. three months pain assessment).

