Most studies on spinal SBRT included a heterogeneous patient population, including previously unirradiated patients, patients who needed reirradiation, and post-operative SBRT, and these categories include patients with or without solitary spine metastases [8, 32]. We include all unirradiated patients with spinal metastases including patients with diffuse metastases, and mild neurological complaints. In this way, we deliberately chose a pragmatic approach since we expect that this would be the patient population that is going to be treated once the benefits of SBRT would have been established. In order to investigate the effect of SBRT without the effect of additional treatments, we however exclude patients who received previous standard or stereotactic body radiotherapy or surgery to the index site. As pragmatic trials investigate the effectiveness of medical treatment strategies under usual conditions, the standard strategy (i.e. 8 Gy in a single fraction, or for selected patients 30 Gy in 10 fractions) will be compared to the SBRT strategy (which includes more dose schedules). Still, the biological effective dose (BED) of the three dose regimen is much higher compared to the BED of the conventional dose regimen. If there is a difference in pain response after SBRT compared to standard radiotherapy, we should be able to detect that differences despite the use of multiple radiation dose schedules. Traditionally, stereotactic radiotherapy in metastatic bone disease is intended for patients with spinal metastases. However, SBRT is increasing being applied in the treatment of non-spine osseous metastases [33]. Since spinal metastases are similar to non-spine osseous metastases in terms of bone involvement and pain relief after standard radiotherapy [34, 35], the response after SBRT in spinal and non-spine osseous metastases is likely to be similar as well. Therefore, we have extended the VERTICAL inclusion criteria to patients with non-spinal bony metastatic disease.

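### Duration of pain response does not end when the index site is re-irradiated or operated on, so a re-treated relapse can count as one unbroken response

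*Protocol article*

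**What the plan says.** All references are to the protocol article.

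- **Primary endpoint:** "Primary endpoint of this study is complete or partial pain response at three months". Both grades of response depend only on pain score and analgesic intake against baseline. For complete response: "A pain score of zero with no concomitant increase in analgesic intake compared to baseline is defined as complete response". For partial response by score: "Partial response is pain reduction of at least two points on a scale of 0–10 without increase in analgesic intake". Progression needs a rise of at least two points above baseline, or at least 25% more analgesic use than at baseline. The scheme is closed: "All responses not captured with complete and partial response or pain progression are considered indeterminate response".
- **Secondary endpoints:** "Duration of pain response starts at response until pain progression or end of follow-up". The information comes from the Brief Pain Inventory (BPI).
- **Data analysis:** duration of response is compared by Kaplan-Meier and log-rank methods. Patients who die within three months, or who cannot supply pain scores and analgesic use, count as non-responders.
- **Background:** after standard radiotherapy, "one in five patients needs re-irradiation".

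No endpoint or analysis rule in the article gives any role to radiotherapy or surgery of the index site after the allocated treatment.

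**The concern.** Duration of response should say how long relief from the allocated treatment lasted. Re-irradiation or surgery of the same site during a response usually means that relief has failed. Under the stated rule it changes nothing, and any relief from the second treatment is added to the duration credited to the first. If re-treatment is more common after standard radiotherapy, control durations are lengthened more than SBRT durations and the log-rank comparison is pulled toward no difference.

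A related question arises at three months: a patient whose first treatment failed, and who was re-treated and then improved before the assessment, counts as a responder in the allocated arm.

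**Working it through.** **1. Does the stated progression rule catch the relapse that leads to re-treatment?** By score, progression requires current pain ≥ baseline + 2.

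- Baseline 8, response at 2, return to 7 on stable analgesics: the threshold is 8 + 2 = 10, and 7 < 10, so there is no progression. If re-treatment then brings pain down again, the response was never interrupted.
- Baseline 9 or 10: the threshold is 11 or 12, which a 0–10 scale cannot reach. These patients can progress only through analgesic use.
- The analgesic route catches some relapses, but the text requires pain to be at least stable, while Table 2 has no such condition. In the 8–2–7 example with 25% more analgesic use, Table 2 gives progression. The text does not, if a score below baseline fails its condition.

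**2. Would the questionnaires show it?** The BPI is given at 2 and 6 weeks, at 1, 2, 3 and 6 months, and every six months thereafter. A relapse at month 8 that is re-treated and better by month 12 falls between two assessments and leaves no trace in the BPI.

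**3. How many patients?** One in five of 55 controls is 0.20 × 55 = 11. Some of these would be patients who never responded and have no response to prolong. The article does not give the split or the timing, so 11 is a ceiling for the control arm and not an estimate. There is no figure for the SBRT arm and none for surgery.

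**4. Three-month endpoint: the plan's own figure first.** Inputs from Sample size considerations: 60% control response, 85% after SBRT, 90% acceptance, one-sided α 5%, power 80%.

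- SBRT arm as randomized: 0.9 × 85% + 0.1 × 60% = 82.5%. Difference: 82.5 − 60 = 22.5 points.
- n = [z₀.₉₅ √(2p̄q̄) + z₀.₈₀ √(p₁q₁ + p₂q₂)]² / (p₂ − p₁)², with p₁ = 0.60, p₂ = 0.825, p̄ = 0.7125.
- n = [1.645 × 0.640 + 0.842 × 0.620]² / 0.225² ≈ 49 per arm, and 49 / 0.9 rounds up to 55. Both planned numbers are reproduced.

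**5. Three-month endpoint: illustration only.** Let r_c and r_t be the shares of the control and SBRT arms that fail first treatment and are re-treated before month 3, and s the share of these who then meet the response rule. The counted difference falls by (r_c − r_t) × s. All three inputs are assumptions; s is taken as 40–60%. Power is for 49 per arm, one-sided 5%.

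| r_c | r_t | Control counted | SBRT counted | Difference (points) | Power |
|---|---|---|---|---|---|
| 0 | 0 | 60% | 82.5% | 22.5 | 80% |
| 5% | 0 | 62–63% | 82.5% | 19.5–20.5 | 70–74% |
| 10% | 0 | 64–66% | 82.5% | 16.5–18.5 | 59–67% |
| 10% | 5% | 64–66% | 84.5–85.5% | 19.5–20.5 | 73–76% |

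The 5–10% for controls corresponds to a quarter to a half of the one in five being re-treated before month 3: 0.20 × 0.25 = 5% and 0.20 × 0.50 = 10%. The loss with no re-treatment in the SBRT arm is then 5 × 0.4 = 2 to 10 × 0.6 = 6 points.

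**The case against.** The strongest objection concerns the primary endpoint. A reader might infer that counting re-treated patients as three-month responders contradicts the trial's own aim, because the Discussion says "In order to investigate the effect of SBRT without the effect of additional treatments". That sentence goes on to exclude patients with earlier radiotherapy or surgery at the index site. It explains an entry criterion and promises nothing about care after randomization. The next sentence describes a pragmatic comparison of strategies under usual conditions, and Data analysis specifies intention to treat. Counting later care within each strategy is a legitimate choice, and this stands.

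A reader might also infer that duration is distorted for the full one in five, or that the trial is underpowered. Neither follows. Only responders have a duration to prolong, and the re-irradiation figure has no time window. The power losses rest on assumed inputs. The 60% control rate comes from a meta-analysis, and the article does not say whether re-treated patients counted as responders there; if they did, part of the effect is already in the 60%. If controls are re-treated more often, the error is also toward no difference and cannot create a false SBRT benefit.

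Last, the cited consensus criteria or the full protocol may contain a re-treatment rule, and neither can be checked here. But the article states when a response ends, rather than leaving that open, and the stated rule gives a wrong duration for a re-treated responder.

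**Conclusion.** The point holds for duration of response. As written, a responder who relapses and is re-treated at the index site can keep one uninterrupted response, because progression is measured above baseline and re-treatment is not an end event. This follows from the text without numerical assumptions. The number affected is unknown: fewer than 11 of 55 controls if the one-in-five figure applies and any of those re-irradiated are non-responders.

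For the three-month primary endpoint there is no error to correct. A supplementary analysis is worth having because the effect of early re-treatment is unknown. It may be small, or 2–6 points toward no difference under the assumptions shown, and less if SBRT patients are re-treated too. If the SBRT arm were re-treated more often, the direction would reverse.

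**What to change.** - **Secondary endpoints:** add re-irradiation or surgery at the index site as an end of response beside pain progression, counted as an event and not censored.
- **Data analysis:** leave the intention-to-treat primary analysis unchanged. Add a prespecified supplementary analysis in which patients re-treated at the index site before the three-month assessment are non-responders, as dropouts already are.
- **Reporting:** give the number re-treated at the index site by arm, before and after three months.

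None of this says when a patient should be re-treated.

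**Cost:** a few sentences and some recoding. The article says follow-up data come from clinical files but does not name re-irradiation, so the team should confirm that its dates are recorded in both arms. Response rates in the supplementary analysis, and durations, will be slightly lower. The main drawback is that treatment is open and re-treatment is a clinician's decision that may depend on the arm. Scoring it as failure could therefore favour one arm, so the revised duration and the supplementary analysis should be read beside the intention-to-treat result and the re-treatment counts.
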